### Part 2: observation

The second part of RTC is an investigation of the level of cultural safety of renal health services. A mixed methods approach will be used to identify and examine patient-, provider-, service- and system-level factors that impact First Nations renal patients’ ability to obtain treatment closer to home.

#### Data collection

Part 2 consists of five steps, which are shown in figure 4.

**Figure 4 F4:**
[figure not shown]
Return to Country—data collection steps.

##### (I) Organisational Cultural Safety Audit

Renal health services will take part in an Organisational Cultural Safety Audit of policies, practices and procedures. The audit tool will highlight areas performing well and areas for improvement. It can be used to monitor change over time. The audit tool is based on the National Safety and Quality Health Service Standards (NSQHSS) User Guide for First Nations Health^38^ and organisational health literacy-related indicators and a section from the Congress of Aboriginal and Torres Strait Islander Nurses and Midwives (CATSINAM) framework.^41^ Senior clinic management staff of each renal service will be invited to complete the audit for their service and study personnel will be available to assist on request.

##### (II) Staff survey and interviews

All staff at each site will be invited to complete an anonymous online staff survey, including medical doctors, registered nurses, allied health staff and any other non-clinical staff employed in the renal health service. The survey asks about their opinions and experiences working in the renal service and looks at patient-, staff-, service- and system-level factors that may impact cultural safety in renal services. Informed by the work of Skinner *et al*,^42^ the survey includes elements from the Modern Racism Scale^43^ and the Attitude Towards Indigenous Australians Scale,^44^ as well as questions about intercultural communication.^45^ Each service will have its own unique link to enable individual participants’ responses to be grouped by service level. If requested, paper copies of the staff survey can be provided. Staff may also elect to participate in a one-to-one interview with study personnel to explore staff survey domains in more detail. The staff survey will be administered by the Social Research Centre, based in Melbourne, Victoria, Australia.

##### (III) ANZDATA registry data

Data will be requested from ANZDATA to provide a 5-year summary of the incidence and prevalence of each dialysis and transplant modality for First Nations and non-First Nations patients at each service. ANZDATA data include centre-specific reports with deidentified patient data related to postcode at entry and at census dates, comorbidities, treatment modalities and outcomes (at entry and throughout the treatment journey) and treatment centre. All renal units in Australia and New Zealand contribute data to the national renal (ANZDATA) registry.

##### (IV) Feedback to staff and key informant interviews

The results from the audit, staff surveys and interviews and ANZDATA registry data will be reported back to senior medical and nursing clinicians. This provides a foundation for renal health service critical reflection and considers areas for improvement. Open group feedback sessions for renal service staff will provide an opportunity for further discussion of results and to identify areas that could be strengthened to improve organisational cultural safety.

Semistructured qualitative key informant interviews will be conducted with key staff at the renal health service to understand the capacity to improve the provision of culturally safe care to First Nations patients. An estimated five key staff can include the Head of Unit, Nursing Director, Aboriginal Health Practitioner/Worker, Social Worker, Aboriginal Liaison Officer, transplant coordinator or other allied health professionals. The interview guide will be informed by findings from the organisational audit and staff survey and include topics related to organisation readiness and implementation barriers and facilitators from the Consolidated Framework For Implementation Research.^46^

##### (V) Talking circles with patients

Feedback of findings will also be provided to First Nations patients to obtain perspectives. First Nations patients with kidney failure and their carers will be invited to attend the talking circles, where results of their service’s organisational audit and staff survey will be presented. Patient sample selection being voluntary and therefore a ‘convenience’ sample of those interested; care will be taken to ensure that transport challenges, disability and/or language needs are met through study funding. With individual patient consent, two talking circles will be conducted over two consecutive days (to accommodate differing prescribed dialysis schedules). The discussions will be recorded and analysed to develop an understanding of patient and carer perspectives about the cultural safety of their renal service.

### Data analysis

#### (I) Organisational Cultural Safety Audit

The organisational policies and procedures audit tool will be completed by renal unit management staff, assisted by RTC study personnel if requested. The completed audit domains will be reviewed by RTC study personnel to determine the extent to which current unit/service documents (including policies, procedures and plans) meet the RTC cultural safety guidelines across the seven domains. For each renal health service, study personnel will provide an audit score over seven domains based on the completed and supporting information provided by senior service staff. The seven domains of assessment are ‘Working in partnership’; ‘Addressing health needs of First Nations people’; ‘Cultural awareness and cultural safety’; ‘Implementation and monitoring’; ‘Governance and identifying priorities’; ‘Welcoming environment’ and ‘Organisational Health Literacy’. A level of cultural safety will be assigned by RTC project personnel to the service for each domain using the categories: ‘action strongly recommended’, ‘should be strengthened’ and ‘performing well’.

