#### Data collection

Follow-up service-level data collection will be repeating steps I–V:

A follow-up organisational audit (with the same tool at baseline) will be conducted a minimum of 1 year after the initial audit measurement to monitor any change in policies and procedures.Using the same methodology and survey tool as the initial staff survey, after a minimum of 1 year service staff will be invited to participate in a repeat staff survey.Additionally, ANZDATA registry data will be obtained to analyse trends and changes in practice and patient outcomes.Staff of participating renal services will be invited to attend a final feedback session(s)All patients, particularly but not exclusively First Nations patients, will be invited to at least one final feedback session at which aggregated, and service-specific study findings. Short videos and posters will facilitate communication of study findings in plain English.

Additionally, process data will be collected from the CoP. These data can include staff and consumer perspectives, planning schedules, implementation strategies, photos or videos of the activities or strategies that are implemented, and recorded reflections.

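### The repeat cultural safety audit, as described, cannot tell a new policy from an existing one first handed in after the service has seen its baseline result

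*Protocol article*

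**What the plan says.** Part 2, step (I), describes who fills in the tool: "Senior clinic management staff of each renal service will be invited to complete the audit for their service". Help from the study team is optional. The corresponding data analysis section has study personnel judge "the extent to which current unit/service documents (including policies, procedures and plans) meet the RTC cultural safety guidelines". The score itself is given "based on the completed and supporting information provided by senior service staff". Each of seven domains then receives one of three ordered labels: "action strongly recommended’, ‘should be strengthened’ and ‘performing well".

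Feedback follows. "The audit tool will highlight areas performing well and areas for improvement", and under step (IV) the audit results, with the staff survey, interview and registry findings, "will be reported back to senior medical and nursing clinicians" before open staff sessions. The Dissemination section adds that each service is given a report of its audit at baseline and at follow-up.

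Part 3, Data collection, states that the follow-up audit uses the same tool and "will be conducted a minimum of 1 year after the initial audit measurement to monitor any change in policies and procedures". Part 3, Data analysis, carries over the Part 2 methods. Table 1 lists the baseline and follow-up audits among the measures for the objective on how far services change their delivery of care. The ANZDATA analysis section says audit scores might also be added to the outcome models.

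**The concern.** The audit is meant to measure the state of a service's documents, but what gets scored is the completed tool plus the material the service supplies. The two coincide only if submission is complete. At baseline, managers meet the tool for the first time and get help only if they ask. By follow-up the service has been told which domains fell short, so the second submission may well be fuller than the first. A policy already in force at baseline but not supplied then would lift the follow-up rating although nothing new had been written.

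At stake is how the audit evidence on service change is read. Better assembly of existing paperwork could be reported as organisational change, most easily in domains thinly documented at baseline. If audit scores enter the outcome models, the same error would affect the baseline covariate. Independent or masked scoring would not cure this, because the problem lies in what reaches the assessor.

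**Working it through.** The article gives no figure for the audit comparison (no effect size, error rate or expected change), so there is nothing to reproduce. The check is to follow the audit through the article.

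1. **Source of evidence.** The audited service's own senior management completes the tool and provides the supporting information (Part 2, step (I), and its analysis section). The article describes no independent document search and no common list of documents to be supplied at both audits.
2. **Order of events.** Baseline audit, then feedback of results to the service (step (IV); Dissemination), then an action plan (Part 3), then the repeat audit after at least one year.
3. **Scoring at follow-up.** Same tool, same method (Part 3, Data collection and Data analysis). There is no rule for dating a document or for re-scoring baseline when an older document turns up.
4. **Interpretation.** The repeat is there to monitor change in policies and procedures, and the pair of audits is a listed measure of service change (Table 1).
5. **Comparison.** Every participating service receives feedback. No group is described as audited twice without it, so a drift in submission cannot be subtracted out.

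A simple identity shows what drives the size. Let a service truly meet a share p of the criteria at both audits, and let it document a share s0 of these at baseline and s1 at follow-up. With no true change:

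apparent change = p × s1 − p × s0 = p × (s1 − s0).

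This is zero only if submission is equally complete both times (or p is zero). It is positive if s1 > s0 and negative if s1 < s0.

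None of these quantities is in the article. With assumed values for illustration only:

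- low: p = 0.4, s1 − s0 = 0.10, giving 0.4 × 0.10 = 0.04 of the criteria;
- high: p = 0.8, s1 − s0 = 0.30, giving 0.8 × 0.30 = 0.24 of the criteria.

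On a three-category scale, a shift of this kind could move a domain that sits near a cut-point up one category.

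For scale, eight targeted services (Study sample) × seven domains = 56 ratings per wave. If an assumed 10% to 30% of baseline ratings were one level too low for this reason, and all were put right at follow-up, then 56 × 0.10 = 5.6 to 56 × 0.30 = 16.8 ratings would rise one level. The percentage is an assumption with no support in the article, so this range is not an estimate of what will happen.

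**The case against.** The strongest reply is that this is audit-manual detail which an article may leave to the full protocol, and that nothing bars study personnel from noticing that a policy is old. That is true of the date rule taken alone. But the article itself fixes the scoring basis, the feedback, the repeat tool and the purpose of the repeat. Followed as written, these cannot separate a new policy from a newly submitted one, so the point is more than an omission.

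Other parts of the reply stand and limit the claim:

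- A reader might infer that the bias is certain and always upward. The documents do not support that. Less effort at a repeat audit, changed management or more self-critical completion after feedback could push the other way at some sites.
- A reader might infer that the plan prespecifies the raw audit difference as its estimate of change. It does not specify an audit difference analysis; the sentence on comparing service-level scores between baseline and follow-up stands under the staff survey.
- Feedback sessions and key informant interviews may bring overlooked policies to light, and staff perspectives on the audit data are to be analysed. Staff surveys, Community of Practice data and patient feedback serve the same objective. This allows triangulation but does not correct the audit score.
- The health-outcome objective rests on ANZDATA data alone, the Part 3 effect model uses the introduction of interventions rather than audit change, and audit scores in the outcome models are only a possibility.
- A strict date rule as the sole definition of change would err too: an old policy newly put into use is real change, and a routine re-issue with a new date is not.

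**Conclusion.** The point holds in a limited form. Because ratings depend on service-supplied material and the repeat follows feedback, an existing policy first submitted at follow-up would raise the rating without a new policy. The likely direction is towards apparent improvement. This rests on the assumption that services submit more fully once they know where they were rated low. How often that happens is not stated and cannot be derived from the article, so neither 0.04 to 0.24 of the criteria nor about 6 to 17 of 56 ratings should be cited as the expected bias. The consequence falls mainly on one of several measures of service change, and only conditionally on the outcome models. It is worth correcting before the follow-up audits, because document dates are easiest to capture at submission.

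**What to change.** In Part 3, Data collection, state that:

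1. the same list of supporting documents is requested at both audits, and each document's issue date or last substantive revision date is recorded;
2. where a document supplied at follow-up pre-dates the baseline audit, the affected baseline item is re-scored with it;
3. the audit change is reported with and without this correction, and a rise explained only by previously existing documents is not interpreted as policy change;
4. undated practices, routine re-issues without change of content, and existing policies newly put into use are shown separately;
5. any outcome model that uses audit scores is repeated with the corrected baseline as a sensitivity analysis.

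The cost is a date field on the audit form, a common request list and re-scoring of the affected items. Some practices cannot be placed in time and will have to be shown as such, and the reported improvement may be smaller.

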#### (II) Staff survey

Concluding each survey period (typically 2 months), deidentified staff survey data will be collated by the Social Research Centre and sent to study personnel using secure methods. A descriptive analysis of cross-sectional staff survey data will first be conducted to describe participant characteristics and provide frequency distributions to each question. For each service, a score across all participants and responses will be derived in total for each domain. Multi-level statistical models incorporating aggregate service-level data (aggregate staff survey tool scores, for example) and individual patient-level clinical and sociodemographic data (clustered at the service level) will be developed. Differences in service-level scores will be compared between baseline and follow-up, and across the different sites.

FDR=Log SIR±Z(α/2)×the bootstrap estimate of the SE of log-SIR.^49^

Ultimately, as noted above, it may be possible to include additional centre-specific data as noted above (including summary staff survey scores and organisational cultural safety audit scores) as explanatory random effects in the statistical models that predict the ‘RTC’ quantitative outcomes of interest.

The Log-SIR along with 95% and 99% FDRs will be presented using funnel plots. The funnel plot shows the log-SIR for each centre against their effective sample size which is a measure of the variability of the SIR estimate. The effective sample size is defined as a measure of the variability of the log-SMRs (logarithm of the standardised mortality ratios) for each centre relative to the total variability of all log-SMRs.^47 48^ It is used as the x-axis for the funnel plots to give smooth curves for the FDR lines.

Both STATA V.18 and R software will be used for quantitative data analysis. It is expected that open source R software code will be published alongside the results of analysis, with each centre publicly deidentified (but privately identified for reports to each centre’s executive, staff and patients about their centre’s involvement in the project). Data shared by ANZDATA for this project will not be able to be published, in line with the standard ANZDATA data release agreement, but could be made available by ANZDATA on request.

#### (II), (IV) and (V) Qualitative data analysis

Because text and image data will be dense and rich, the qualitative data analysis will require sequential steps to be followed, involving multiple levels of analysis. Qualitative data from staff interviews, key informant interviews and feedback circles will be translated (as needed) and transcribed verbatim—with or without annotations for behaviour (eg, pausing, laughing, crying); field notes will be typed up, visual and audio material will be catalogued and sorted to read or look at. This will be a collaborative process involving First Nation researchers and will yield a general sense of the information, providing an opportunity for reflection before a process of coding using both inductive and deductive coding approaches. NVivo software will be used to manage and analyse the qualitative data where appropriate. The representing of the description and themes will be represented by using narrative passages to convey the findings for discussion, as in grounded theory. There will be separate analysis for Study Parts 1–3.

For example, to understand the factors associated with renal health disparities that is, in relation to transplantation and dialysis treatment experienced by First Nations patients compared with non-First Nations patients, a range of methods will be used to enable triangulation of data across multiple sources and perspectives. Thematic and content analysis of service staff perspectives about the organisational audit data, staff survey data and ANZDATA outcomes data will potentially highlight staff-level factors contributing to renal health disparities and provide a richer understanding of the organisational policy audit score.

Qualitative techniques used for analysis:

grounded theory techniques—using open-ended questions in interviews and surveys, studying archival data (eg, ANZDATA registry outcome data);content analysis—using the presence of certain words, themes and/or concepts within the transcribed interview; andnarrative analysis —used to understand the differences in cases and describing context.

### Part 3: implementation

The third part of RTC involves the Community of Practice (CoP), site committee and the leadership group working together with volunteer RRT patients who come together seeking to understand the patient experience and the possible correlation to patient outcomes in the renal unit. RTC personnel will work with renal health service staff to form a working group and/or help facilitate a workshop to develop an action plan to enhance the provision of culturally safe care to First Nations renal patients and help increase the number of renal patients receiving treatment closer to home. The renal service committee will be responsible for communication at service level and the development of the intervention strategies. The establishment of the CoP may provide an ongoing mechanism via which patient and community can feedback on their experiences and suggestions which can be used by the renal service to improve service provision. Members of the CoP will include renal patients, community members and renal health practitioners. They develop a shared repertoire of resources: experiences, stories, tools, ways of addressing recurring problems—in short, a shared practice.

#### Data collection

Follow-up service-level data collection will be repeating steps I–V:

A follow-up organisational audit (with the same tool at baseline) will be conducted a minimum of 1 year after the initial audit measurement to monitor any change in policies and procedures.Using the same methodology and survey tool as the initial staff survey, after a minimum of 1 year service staff will be invited to participate in a repeat staff survey.Additionally, ANZDATA registry data will be obtained to analyse trends and changes in practice and patient outcomes.Staff of participating renal services will be invited to attend a final feedback session(s)All patients, particularly but not exclusively First Nations patients, will be invited to at least one final feedback session at which aggregated, and service-specific study findings. Short videos and posters will facilitate communication of study findings in plain English.

Additionally, process data will be collected from the CoP. These data can include staff and consumer perspectives, planning schedules, implementation strategies, photos or videos of the activities or strategies that are implemented, and recorded reflections.

#### Data analysis

Data analysis will follow steps I–V as described in Part 2. Multi-level logistic or Poisson regression methods will be used for the analysis of the effect of interventions, clustered by the centre and analysed at the individual level, with the introduction of one or more interventions incorporated as time-dependent variables.

##### Process evaluation

Process data will be critically reviewed throughout the project to identify any barriers and facilitators to change and inform changes in project methods and processes to maintain research rigour and study integrity.

##### Mixed methods analysis

Qualitative and quantitative data will be analysed, synthesised and integrated to provide a comprehensive understanding of overall project impacts and outcomes.^50^,^52^

In summary, both patient-reported experience, as well as patient-level registry, service-level aggregate staff survey data and policy audit data will be collected to meet the objectives of the study. See table 1.

**Table 1 T1:** Study objective and measures

Objective	Measures and tools (data collection)
To test the feasibility and appropriateness of a patient survey adapted for First Nations peoples (both in English and several First Nations languages)	Adapted video reflexive ethnography and evaluation of patient and interpreter feedback
To understand the factors associated with renal health disparities (ie, in relation to transplantation and dialysis treatment) experienced by First Nations patients compared with non-First Nations patients.	Staff survey ANZDATA registry data Organisational audit Qualitative interviews with renal service staff
To assess the level of cultural safety among renal health services and their staff from the patient experience perspective	Patient perspectives via feedback session
To identify the barriers and enablers for organisational change in relation to the provision of culturally safe care to First Nations patients with kidney failure	Community of Practice process data (see above) Qualitative interviews with renal service staff and key informant interviews
To assess and evaluate the extent to which health services change their delivery of care to First Nations patients with kidney failure following an assessment of their level of cultural safety	Community of Practice data (this can include staff and consumer perspectives, planning schedules, implementation strategies, photos or videos of the activities or strategies that are implemented, and recorded reflections.) Baseline and follow-up organisational audits Baseline and follow-up staff surveys Patient perspectives via feedback session
To assess the impact of the renal health service-based changes on health outcomes for First Nations patients with kidney failure	ANZDATA registry data

